### Conditions

#### PA traditional style condition

The PA-TS condition will be composed of twenty sessions of Nordic walking over ten weeks. Participants will walk twice a week in a group of twelve people. Each session will last 60 min, including welcome, warm-up, practice, cool-down and stretching. The instructor of the PA condition (a bachelor’s degree student in sports sciences) will have been trained to teach Nordic walking to beginners as this physical activity is taught in textbooks [71]. We called this condition ‘traditional’ because the instructor will only be trained to teach the correct walking technique and will not receive any training to support the basic psychological needs of participants. He/she will receive a program plan describing the warm-up, cool-down and stretching exercises, places and the duration of the Nordic walking itself for each session.

#### PA need-supportive style condition

In the PA-NSS condition, the organization and content of the session will be identical to the PA-TS condition. The main difference will be the motivational style implemented by the instructor. Two bachelor’s degree students in sport sciences will be both trained to deliver Nordic walking sessions using a need-supportive communication style. Grounded in SDT, the training will consist of four one-hour sessions based on SDT training [42, 72, 73] used in previous studies. In these workshops, instructors will be introduced to the main SDT postulates, will analyze video examples to identify strategies that are supportive to, and those which might frustrate, participants’ needs, and will create strategies to support participants’ needs in Nordic walking with the help of a research team member. For example, instructors will be trained to implement need-supportive strategies, such as: providing choice (e.g. type of exercise, intensity, place, route), encouraging participant input, feedback and questions; giving meaningful explanations; being empathetic and acknowledging difficulties, negative feelings or objections; being accessible, attentive and caring; trying to motivate by promoting enjoyment and the personal value of exercise or giving precise and positive feedback.

#### Theatre condition

The Theatre condition will be composed of twenty sessions of theatre classes over ten weeks (twice a week), in a group of 15 people guided by a master’s degree student in performing arts. Each session will last 60 min, and begin with warm-up voice exercises followed by oral, theatre or improvisation exercises. The theatre sessions will include public speaking games, exercises to use the body according to context and emotions, breathing and pronunciation exercises, confidence exercises in pairs, and an introduction to improvisation exercises.

#### Waiting list control condition

During the ten weeks of the three interventions, participants in the WLC condition will not carry out an activity. They will be contacted each week by email to complete an online questionnaire assessing measures similar to those for the three other groups. At the end of the period, they will be offered the possibility of starting the intervention in a delayed group the following year.

### Measures

Table 1 provides an overview of the measurement points of the primary and secondary outcomes, mediators, moderators and control variables, and manipulation check variables. At the end of the second session of each week, participants will complete a questionnaire measuring their weekly burnout, vigor, needs satisfaction at work and workload, as well as recovery mechanisms experienced, affects and effort perception during sessions (only for the 3 intervention groups). Five minutes are requested to complete the questionnaire. In week six of the program, participants will complete an online survey measuring job characteristics, and intervention groups will wear a 3-axis accelerometer to assess their energy expenditure during PA or theatre sessions. In week eight of the intervention, all instructors will be recorded audio-visually and participants will complete an online survey assessing their instructor’s motivational style during the sessions. At the beginning of the final session of the intervention participants will replicate the cardiorespiratory fitness test, and at the end of the intervention, participants will complete an online survey measuring the same variables as those assessed at baseline. Finally, three and six months after the end of the intervention, participants will be invited to complete the follow-up online questionnaire. In order to measure the *compliance* to the program, instructors from the three intervention groups will be asked to indicate the participants’ presence or absence at each session in a register.

**Table 1 Tab1:** Overview of the measurement points for the primary and secondary outcomes, during intervention and weekly measures, and follow-up measurements

	Variables	Pre-intervention (T0)	During intervention (T6 or T8)	Weekly (T1-T10)	Post-intervention (T11)	Follow-up at 3 and 6 months (T12–13)
Primary outcomes	− Burnout	✓		✓	✓	✓^a^
	− Vigor	✓		✓	✓	✓^a^
Secondary outcomes	− Job satisfaction	✓			✓	✓^a^
	− Work motivation	✓			✓	✓^a^
	− Work performance	✓			✓	✓^a^
	− Work ability	✓			✓	✓^a^
Psychological and physiological mediators	− Off-job recovery activities	✓			✓	
	− Psychological detachment	✓		✓^a^	✓	
	− Relaxation	✓		✓^a^	✓	
	− Control	✓		✓^a^	✓	
	− Mastery	✓		✓^a^	✓	
	− Relatedness	✓		✓^a^	✓	
	− Positive Affects			✓^a^		
	− Cardiorespiratory Fitness	✓			✓	
Moderator variable	− Compliance to activity sessions			✓^a^		
Control variables	− Job characteristics	✓	✓(T6)	✓^b^	✓	
	− Needs satisfaction at work	✓	✓(T6)	✓	✓	
	− Workload at work			✓		
Manipulation check	− Instructors observed motivating style		✓(T8)			
	− *participants’ perception of the instructor’s motivating style*		✓(T8)			
	− Objective effort during sessions		✓(T6)			
	− Perceived effort during sessions			✓^a^		

^a^Variables only collected in intervention groups; ^b^Variables only collected in the waiting-list group

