**Methods:**

Employees of the authors’ University (*N* = 140) will be recruited via email, leaflets, and posters. Participants will be randomized to one of the four arms of the trial: (1) Physical Activity Traditional Style, (2) Physical Activity Need-Supportive Style, (3) Theatre condition, and (4) Waiting List Control. The experimental phase will last 10 weeks, followed by a six-month follow-up. During the ten weeks of the intervention, all groups – except the waiting list control – will carry out two activity sessions per week. Primary outcomes are burnout and vigor, secondary outcomes are work motivation, job satisfaction, work performance and work ability. These variables will be assessed before and after the intervention, and at three and six months after the end of the intervention. Moreover, burnout, vigor, needs satisfaction at work and psychological mediators will be assessed weekly throughout the intervention period.

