### Statistical analysis

#### Analyses of Primary and secondary outcomes

Between-arm differences in changes on the primary and secondary outcomes will be analyzed using generalized linear mixed models (GLMM) according to intention-to-treat and per-protocol principles. Intention-to-treat analyses [91] refer to the effect of treatment “as assigned”, meaning that all participants who are randomized to a condition will be included in the analyses, regardless of dropout or missing values. By contrast, per-protocol analyses refer to the effect of treatment “as received”, excluding only participants who have less than 50% compliance to the 20 sessions in the intervention. GLMM has several advantages over repeated measures ANOVA as it considers the hierarchical nature of the data and can accommodate missing data [92]. To distinguish between short- and long-term intervention effects, two separate series of GLMM analyses were performed for each outcome variable. Two time points (pre and post) were used to determine short-term intervention effects and four time points (pre, post, three- and four-month follow-ups) were used to examine long-term intervention effects. Regarding the short-term intervention effects, differences in changes on the outcome variables as a function of the group allocation will be assessed with models including group, time, and group x time interaction as fixed effects. For the group allocation, contrasts analyses [93] will also be carried out to test our hypotheses (H1 – H4) specifically. For that, three contrasts will be computed. The first one will compare the WLC condition with the Theatre condition, PA-TS and PA-NSS conditions (respectively coded as − 0.75, + 0.25, + 0.25, + 0.25) to test whether doing a leisure activity (PA or Theatre conditions) at the workplace leads to a reduction in burnout and an improvement in vigor (H1a, H1b). The second contrast will compare the Theatre condition with the PA-TS and PA-NSS conditions (respectively coded as − 0.667, + 0.333, + 0.333, while WLC will be coded 0) to test whether PA is more effective than theatre condition (H2) in reducing burnout and improving vigor. Finally, the third contrast will compare the PA-TS condition with the PA-NSS condition (respectively coded as − 0.50, + 0.50, while WLC and Theatre conditions will be coded 0) to test whether the positive effect of PA is more pronounced when the instructor uses a need-supportive style (H3). The same analyses will be performed to examine if the effects of the intervention are still effective three months (T12) and six months (T13) after the end of the intervention period. Since there are more than two-time measurements per participant, we will allow random intercepts for participants and random linear slopes for the repeated measurements at the level of participants. These random effects will allow us to estimate each participant’s outcome variables and the rate of change of these outcomes over time. In all analyses we will control for a number of variables that could influence participants’ outcomes. These include job characteristics, and needs satisfaction-frustration at work. Finally, an estimate of the effect size for each outcome will be reported using the conditional pseudo R^2^, which will be computed using the MuMin package of the R software [94].

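### Table 1 collects the 3- and 6-month outcomes only in the activity arms, while the long-term analysis repeats the waiting-list contrast at those times; the sections conflict and must be reconciled

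*Protocol article*

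**What the plan says.** Table 1 (Measures) has a column headed "Follow-up at 3 and 6 months (T12–13". In it, both primary outcomes and all four secondary outcomes (job satisfaction, work motivation, work performance, work ability) carry superscript a, whose footnote reads "Variables only collected in intervention groups". The same six outcomes carry no superscript at T0 or T11, and weekly burnout and vigor carry none either.

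The section on analyses of primary and secondary outcomes defines three contrasts. Of the contrast that serves H1a and H1b it says: "The first one will compare the WLC condition with the Theatre condition, PA-TS and PA-NSS conditions". On the long term it says: "The same analyses will be performed to examine if the effects of the intervention are still effective three months (T12) and six months (T13". No sentence removes WLC or this contrast from the long-term models. The same section lists the long-term visits as "four time points (pre, post, three- and four-month follow-ups".

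Two places describe follow-up without limiting the arms. The Abstract says "These variables will be assessed before and after the intervention, and at three and six months after the end of the intervention", and the Measures text says "three and six months after the end of the intervention, participants will be invited to complete the follow-up online questionnaire". The waiting-list section says that these participants will be "offered the possibility of starting the intervention in a delayed group the following year"; it gives no reason to stop collecting their outcomes at T11.

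**The concern.** The first contrast is the only one that sets doing an activity against doing none. Read with Table 1, the long-term analysis asks for that contrast at two visits where one side of it is not measured. A claim that benefit over control persists at 3 or 6 months, on either primary outcome or on the secondary outcomes, would then have no control observations behind it at those visits. Depending on how time enters the model, the software would either fail to estimate the contrast or return a figure that gives no sign of this.

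**Working it through.** **Inputs**
- Arms measured at T12 and T13: Table 1 and its footnote.
- Contrast 1 codes: WLC −0.75, each activity arm +0.25 (analysis section). The codes are one unit apart, so the coefficient is the mean of the three activity arms minus WLC.
- 35 per group and a correlation of 0.5 between repeated measures (Sample size).
- Assumed here: T11 at week 10, T12 at week 10 + 13 = 23, T13 at week 10 + 26 = 36; outcome SD of 1; no dropout; a random-intercept working model.

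The plan gives no figure for the long-term contrast. Its total of 140 belongs to the short-term question. A group-by-time interaction with 4 groups, 2 time points, f = 0.175, alpha 0.025, power 80% and correlation 0.5 needs 111, which is 112 in equal groups, and 112 × 1.25 = 140.

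**Step 1. Cells with data in the four-time-point model, if Table 1 is followed**

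| Arm | T0 | T11 | T12 | T13 |
|---|---|---|---|---|
| PA-TS | yes | yes | yes | yes |
| PA-NSS | yes | yes | yes | yes |
| Theatre | yes | yes | yes | yes |
| WLC | yes | yes | no | no |

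**Step 2. Categorical time.** There are 4 × 4 = 16 arm-by-time means, of which 14 have data, so the design has rank 14 of 16. Contrast 1 at visit t is the mean over the activity arms of (mean at t − mean at T0), minus the same change in WLC. At T12 and T13 it needs the two empty cells, so it is estimable at T11 only. Contrasts 2 and 3 give WLC a weight of 0 and are estimable at every visit. If WLC is followed, the rank is 16 of 16 and all three contrasts are estimable throughout.

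**Step 3. Linear time.** The WLC line is fitted on T0 and T11 and extended.
- Coded in weeks: 23/10 = 2.3 and 36/10 = 3.6 times the observed change.
- Coded by occasion (0, 1, 2, 3): 2/1 = 2 and 3/1 = 3 times.

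**Step 4. Precision with linear time in weeks.** In one arm, Var(slope) = (1 − ρ)/(n × Sxx).
- Weeks 0 and 10: Sxx = 50. Weeks 0, 10, 23 and 36: mean 17.25, Sxx = 734.75.
- WLC as in Table 1: 0.5/(35 × 50) = 0.000286. One activity arm: 0.5/(35 × 734.75) = 0.0000194; mean of three arms: 0.00000648.
- Without WLC follow-up: sum 0.000292, SE 0.01709 per week. Multiplied by 23 this is 0.393 SD; by 36, 0.615 SD.
- With WLC follow-up: 0.0000194 + 0.00000648 = 0.0000259, SE 0.00509 per week. Multiplied by 23 this is 0.117 SD; by 36, 0.183 SD.
- With WLC follow-up and categorical time: the variance of a change is 2(1 − 0.5) = 1, so SE = √[(1/35)(1 + 1/3)] = 0.195 SD at each visit.

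The 0.615 SD covers sampling error only. It does not include the error made if the WLC course after week 10 is not a straight line.

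**The case against.** The strongest reply is that the superscript is misplaced. The Abstract and the Measures text do not restrict follow-up to the activity arms, and Table 1 is not footnoted carefully throughout: perceived instructor style at T8 and objective effort at T6 carry no superscript a, although WLC has neither instructor nor sessions. This stands to the extent that a table error cannot be excluded. A reader might infer that leaving WLC unfollowed is a settled design decision; the documents do not establish that. But six matching superscripts look deliberate, and the Measures text uses the word participants loosely. If the table is the error, it still has to be corrected.

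A second reply is that the section cites the ability of mixed models to accommodate missing data. That does not help when a whole arm is unobserved by design. Nor can a later analysis plan recover data that were not collected; it could only drop the contrast.

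Other replies do limit the point:
- A reader might infer that the model will extrapolate by a factor of 3.6. The section specifies random linear slopes per participant but does not say whether the fixed effect of time is linear or categorical, nor how it is coded. Asking about T12 and T13 separately fits categorical time, where no extrapolated figure arises.
- A reader might infer that WLC is measured only twice. It also gives weekly three-item burnout and vigor ratings at T1 to T10. These end at week 10 and do not fill the gap.
- A reader might infer from the four-month wording that the model places the last visit at the wrong time. The same section ties T13 to six months and gives no numeric time code, so this is a wording slip.

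**Conclusion.** The point holds as an internal contradiction that decides whether a long-term comparison with control is possible. If Table 1 governs, contrast 1 at T12 and T13 is either not estimable (categorical time) or rests wholly on projecting the WLC change of the first 10 weeks (linear time). Under the stated assumptions, the week-36 standard error then rises from 0.183 to 0.615 SD, about 3.4 times, and exceeds the effect of 0.35 used for planning. The multipliers and standard errors depend on the assumed visit timing, coding, working model and absence of dropout; the lack of control data does not.

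The scope is limited. What is affected is long-term H1a and H1b, and the part of H4 that refers to WLC. A reader might infer that the trial's main comparison fails. It does not: the pre-post WLC comparison, for which the sample size reproduces, is intact, and contrasts 2 and 3 (H2, H3) can be estimated at every visit.

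**What to change.** Choose one and make the sections agree.

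**(a) Follow WLC.** Remove superscript a from the six T12–13 cells, state that WLC completes both follow-ups, and send it the same online questionnaire. Use WLC data only up to the start of any delayed programme; the article gives no calendar dates, so say whether that start can fall before T13. Estimate contrast 1 at each visit from data observed at that visit. Cost: two online questionnaires to about 35 people, roughly 70 in all, in an arm already emailed weekly. This is possible only while follow-up is open.

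**(b) Do not follow WLC.** Remove WLC and contrast 1 from the long-term models, keep contrasts 2 and 3, and state that no long-term comparison with control will be made. Cost: wording only, but the claim of lasting benefit over no activity is given up.

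Under either option, correct the four-month wording in the analysis section so that it agrees with T13 at six months.

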#### Primary outcomes

##### Burnout at work

*Burnout* will be assessed with the French version [74] of the SMBM [5]. The scale consists of 14 items divided into three subscales: *physical fatigue* (e.g., “I feel physically drained”), *cognitive weariness* (e.g., “I feel I’m not thinking clearly”), and *emotional exhaustion* (e.g., “I feel I am not capable of investing emotionally in coworkers and customers”). Scores are rated using a seven-point Likert scale (1 = never; 7 = always). In prior research, the English [22, 75, 76] and French [74] version of the SMBM has proved to be a valid and reliable instrument to assess burnout. Using data from the baseline measurements, we will select the three most representative items according to their loading on each of the three factors to assess weekly burnout.

##### Vigor at work

V*igor* will be measured with the French version [77] of the SMVM [7]. The scale consists of 12 items divided into three subscales: *physical strength* (e.g., “I feel I have physical strength”), *cognitive liveliness* (e.g., “I feel able to be creative”), and *emotional energy* (e.g., “I feel able to show warmth to others”). Scores are rated using a seven-point Likert scale (1 = never; 7 = always). In prior research, the English [78–80] and French [77] version of the SMVM has proved to be a valid and reliable instrument to assess vigor at work. Using data from the baseline measurements, we will select the three most representative items according to their loading on each of the three factors to assess weekly vigor.

#### Secondary outcomes

##### Job satisfaction

To measure employees’ job satisfaction the five items from the Global Professional Life Satisfaction scale [81] will be used. This scale measures overall job satisfaction as felt by the individual with a seven-point scale (1 = strongly disagree, 7 = strongly agree) (e.g., “I’m satisfied with my professional life”). Studies have reported good reliability and validity of this scale [81, 82].

##### Work motivation

To measure employees’ work motivation we will use the French version of the Motivation at Work Scale [83]. The scale consists of four subscales of three items: *intrinsic motivation* (e.g., “I do this job for the moments of pleasure that this job brings me”), *identified regulation* (e.g., “I do this job because this job fulfils my career plans”), *introjected regulation* (e.g., “I do this job because my reputation depends on it”) and *external regulation* (e.g., “I do this job for the paycheck”). Scores will be rated on a 7-point Likert scale (1 = totally disagree; 7 = totally agree). The reliability of this scale has been demonstrated by confirmatory factor analyses and evidence for validity was satisfactory [83].

##### Work performance

Global work performance will be assessed with an item from the World Health Organization Health and Work Performance Questionnaire (WHO HPQ; [51]), “How would you rate your overall performance on the days you worked during the past 7 days?” (0 = the worst anyone can do, 10 = the very best that top workers in a job like yours can do). A single item such as this has been used in similar studies [54].

##### Work ability

Work ability will be measured with a single item [49]: “Can you indicate how you rate your current work ability when you compare it with your lifetime best?” (0 = completely unable to work, 10 = work ability at its best). This item has been identified as a good alternative to more exhaustive measures of work ability [49] and has been used in a similar study [66].

#### Psychological and physiological mediators

##### Off-job recovery activities

To identify whether participants engage during their free time in activities with recovery potential - including those proposed in the study - we will ask them to answer the following question, “How often did you spend your time doing this off-job activity, in the last four weeks?” (1 = never, 7 = 6–7 times per week). We will focus on the four activities the most related to well-being and recovery [33, 84]: low-effort activities (e.g., watching TV, lying on the sofa), social activities (e.g., meeting others, making a phone call in order to chat), physical activities (e.g., keep-fit, cycling, dancing), and creative and expressive activities (e.g., theatre, playing music, singing). Then, following the procedure used by Korpela and Kinnunen [84], we will ask the participants, “How effective for recovery from work is the time spent on this off-job activity?” (1 = not at all effective, 7 = highly effective).

##### Psychological recovery experiences

To accurately identify the psychological experiences that may underlie the recovery process, we will use a French adapted version of the Recovery Experience Questionnaire (REQ; [55]). Participants will have to answer to the stem: “In the last 4 weeks, to what extent would you say that the activities you did during your free time (those identified above), enabled you […]”. The items comprise four dimensions: *psychological detachment* (4 items, e.g., “[…] to forget work”), *relaxation* (4 items, e.g., “[…] to kick back and relax”), *control* (4 items, e.g., “[…] to decide for myself what to do”), and *mastery* (4 items, e.g., “[…] to learn new things”). In order to assess the *experience of relatedness* [58], the REQ items will be completed with a French adapted version of the relatedness subscale of the Balanced Measure of Psychological Needs [85] (4 items, e.g., […] to feel close and connected with one or more people who participated with you in these activities). The answers will be provided on a Likert-type scale ranging from (1) *strongly disagree* to (7) *strongly agree*. Factorial validity and reliability will be tested in a pilot study. Using data from the baseline measurements, we will select the most representative items of each of these five dimensions according to their loading on each of the five factors to assess weekly psychological recovery experiences (see below).

